**Methods:**

We will test the hypothesis that topical natamycin 5% in combination with chlorhexidine 0.2% is superior to topical natamycin 5% alone in a two-arm, single-masked RCT (ISRCTN, ISRCTN87195453, registered 27/08/2020,
https://www.isrctn.com/ISRCTN87195453). Participants are adults with FK presenting to tertiary ophthalmic hospitals in Tanzania and Uganda. Baseline assessment includes history, examination, photography, in vivo confocal microscopy and corneal scrapes for microbiology. Participants will be randomised to alternative topical antifungal treatments (topical chlorhexidine 0.2% and topical natamycin 5%; 1:1 ratio, 2-6 random block size). Patients will be reviewed at days 2, 7 (with re-culture), 14, 21, month 2, and month 3. The primary outcome is best spectacle corrected visual acuity (BSCVA) at three months. Primary analysis (intention-to-treat) will be by linear regression, with treatment arm and baseline BSCVA pre-specified covariates. Secondary outcomes include epithelial healing time, scar/infiltrate size, ulcer depth, hypopyon size, perforation and/or therapeutic penetrating keratoplasty, and positive re-culture rate.

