^. This trial found that patients receiving natamycin 5% had significantly better best spectacle-corrected visual acuity (BSCVA) at 90 days compared to those receiving chlorhexidine 0.2% (estimated mean difference in vision - -0.30 logMAR; 95% confidence interval [CI], -0.42 to -0.18; P < 0.001), providing evidence that natamycin 5% is superior to chlorhexidine 0.2%
^
16
^. Patients treated with chlorhexidine healed 39% more slowly than those treated with natamycin (P < 0.001). However, there was no significant difference in the re-culture positivity rate at day-7 between arms (P=0.233).

It is worth noting that there is substantial global variation in the pattern of fungal species causing fungal keratitis
^
2
^. Specifically, Nepal and East Africa exhibit distinct fungal aetiology patterns, limiting the generalisability of the Nepal study to the African context. For instance, in Nepal, the majority of causative organisms were Curvularia spp. compared to Fusarium spp. in Uganda and Tanzania
^
2,
16–
18
^. Moreover, there might be differences in fungal susceptibility profiles and patients’ immunogenetic responses between the two regions.

While natamycin 5% showed promising results in our recent trial in Nepal, several key considerations arise. Firstly, natamycin is not routinely available in East Africa, and even when it is, it is financially out of reach for many patients. Secondly, the trial in Nepal excluded all patients who were receiving or had recently received topical treatment with antifungals. Over 100 patients were excluded from recruitment as they were already on topical antifungal treatment (primarily natamycin 5%) and were mostly attending the tertiary referral centre due to deteriorating condition despite ongoing treatment. These patients sought second-line agents to treat their infection, presenting an ongoing challenge. Thirdly, we conducted a case series in Uganda of 13 patients with fungal keratitis who were failing treatment with natamycin 5%. These patients received adjunctive chlorhexidine 0.2%. Among the 12 who completed three months of follow-up, 9/12 (75%) healed with corneal scarring. The vision was 6/18 or better in 5 of these patients (41.7%)
^
19
^. A tertiary referral eye hospital in the UK employs chlorhexidine 0.2% in patients with severe filamentous fungal keratitis in addition to natamycin 5% monotherapy
^
20
^.

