### Sample size considerations

The study is designed to test the hypothesis that natamycin combined with chlorhexidine is superior to natamycin alone in improving the primary outcome (BSCVA at 3 months). Assuming a BSCVA of 0.5 logMAR in the natamycin-only group, a standard deviation of 0.62 in both groups, and an adjusted alpha of 0.0492 (to accommodate interim analysis using the O’Brien-Fleming method), a sample size of 304 ensures 80% power to detect a 0.2 logMAR improvement. Allowing for a 15% dropout rate, the total target enrollment is 358 participants across both sites. 

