### Analysis plan

An intention-to-treat (ITT) approach will be used, analyzing all data based on the assigned randomisation group, regardless of adherence to the treatment protocol. Analyses will follow CONSORT guidelines for non-inferiority trials
^
35
^, and a flowchart will summarize recruitment, randomisation, and follow-up by treatment arm. Baseline characteristics will also be summarized. Details of the SPIRIT checklist are provided as Extended Data and available online (see Data Availability Statement). 

**
*Primary outcome analysis – unadjusted*
**

The primary outcome (BSCVA at 3 months) will be analyzed using linear regression, including baseline BSCVA and treatment arm as covariates. Mixed fungal and bacterial infections identified at baseline will be excluded from the primary analysis. We will use our alpha of 0.0492 to test the null hypotheses at 0.0492 significance. Significance will be assessed using a two-tailed test at 0.0492 level for assessing superiority.

**
*Primary outcome analysis – adjusted*
**

If baseline covariate imbalances occur between treatment arms, adjusted analyses will be conducted to ensure treatment effects are not confounded by these differences. This is particularly important if natamycin + chlorhexidine has a better outcome than natamycin, as the adjusted treatment effects may account for this observed imbalance whilst the unadjusted analyses may not. Sensitivity analyses will allow us to show that any observed positive treatment effect is not solely explained by imbalances at baseline in any of the covariates.

**
*Secondary analyses of the primary outcome*
**

- Per-Protocol Analysis: Re-analysis will be conducted excluding participants with significant deviations, poor adherence (<50%), or mixed/non-fungal infections. 

- Mixed Infections: Secondary analyses will include mixed infections using the same methodology as the primary analysis. 

- Sensitivity Analyses: Missing data will be addressed through multiple imputation or non-random missing data models if necessary. Additional sensitivity analyses will assess outcomes in subgroups such as those with severe vision loss, corneal perforation, or therapeutic keratoplasty. 

**
*Analysis of other determinants for success*
**

Logistic regression models will identify factors associated with poor outcomes (BSCVA >1.0 logMAR), adjusting for trial arm. Multivariate models will refine predictors based on likelihood ratio tests. 

**
*Secondary outcome analysis*
**

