Time to full epithelial healing (slit lamp examination by ophthalmic clinician)	The time to re-epithelialization will be calculated as the midpoint between the last review showing an epithelial defect (ED) and the subsequent review where no ED is observed. Fluorescein staining covering an area smaller than 0.5 mm will be considered indicative of a resolved ED, given the challenge of distinguishing smaller defects from pooling in healed areas. Time-to-healing analysis will utilize Cox proportional hazards regression, with treatment group as the primary predictor and baseline ED size (geometric mean in mm) included as a covariate. Survival curves for treatment groups will be plotted using Kaplan-Meier analysis up to the three-month endpoint. The proportional hazards assumption will be tested by stratifying baseline ED size into quartiles. If this assumption is not met, stratified results will be reported. Treatment failure (defined as an ED larger than 0.5 mm at the three-month review) will be compared between groups using Fisher’s exact test.
Rate of healing	The rate of ulcer size reduction will be evaluated by measuring changes in ED size over time intervals (1 week to 3 weeks, and 3 weeks to 3 months) and dividing by the number of days, producing a rate (mm/day). This will be analyzed using Cox regression.
Microbiological cure	For patients with persistent corneal ulcers (defined by ED presence) at day 7, a repeat corneal scrape and microbiological tests will be conducted. Microbiological cure at day 7 will be defined as the absence of growth on culture. Cure rates will be compared between treatment arms using logistic regression, adjusting for organism type (e.g., *Aspergillus spp.*, *Fusarium spp.*, or other).
Ulcer depth at 1 week and 3 weeks (slit lamp examination by ophthalmic clinician).	Depth of corneal ulcers (expressed as a percentage of healthy cornea thickness) will be compared between treatment groups at one week and three weeks. This analysis will adjust for baseline ulcer depth using linear regression.
Hypopyon height at 1 and 3 weeks, (slit lamp examination by ophthalmic clinician)	Hypopyon height (in mm) at one and three weeks will be compared between groups, adjusting for baseline height using linear regression.

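### Cox regression on midpoint-dated healing times ignores the interval censoring, so any true effect on healing is estimated too close to 1: a cheap improvement to a secondary outcome

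*Protocol article*

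**What the plan says.** In the protocol article, the Table 4 row on time to full epithelial healing dates each healing as "calculated as the midpoint between the last review showing an epithelial defect (ED) and the subsequent review where no ED is observed". It continues: "Time-to-healing analysis will utilize Cox proportional hazards regression", with arm as the main predictor and baseline epithelial defect (ED) size as covariate. For display, "Survival curves for treatment groups will be plotted using Kaplan-Meier analysis up to the three-month endpoint". How ties are handled is not stated. The same row compares failure to heal by three months with Fisher's exact test.

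The abstract gives the schedule: "Patients will be reviewed at days 2, 7 (with re-culture), 14, 21, month 2, and month 3". Table 3 labels the last two visits day 60 and day 90.

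Table 5 lists time to full epithelial healing first among the key secondary outcomes. The protocol states no target HR, event count or power for it, and no order of testing.

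**The concern.** A slit-lamp visit shows only whether the defect has closed by that day. Each healing time is therefore known only to lie between two visits, and the last two gaps are 39 and 30 days wide. The planned Cox model treats the imputed dates as exact. With visits on schedule, some 300 patients share six event times, and a Cox model with that many ties shrinks the log HR when the arms really differ.

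At stake is the size of a reported secondary effect. The introduction cites slower healing on chlorhexidine as a main result of the earlier Nepal trial, so this HR will probably be read beside that one. An attenuated estimate would understate a real difference and make it easier to miss. The Kaplan-Meier curves would also step at artificial dates.

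**Working it through.** **1. The plan's own figure.** The only stated sample size concerns visual acuity, not healing. With SD 0.62, difference 0.2, "an adjusted alpha of 0.0492" (two-sided) and 80% power, n per arm = 2 × (1.967 + 0.842)² × 0.62² / 0.2² = 151.6, so 152 per arm and 304 in all. Then 304 / 0.85 = 357.6, so 358. Both figures reproduce. The 304 is used below only as the number of patients analysed.

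**2. Intervals.** From Table 3:

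| Interval (days) | Width | Midpoint |
|---|---|---|
| 0-2 | 2 | 1 |
| 2-7 | 5 | 4.5 |
| 7-14 | 7 | 10.5 |
| 14-21 | 7 | 17.5 |
| 21-60 | 39 | 40.5 |
| 60-90 | 30 | 75 |

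**3. Why grouping shrinks the HR.** Take one interval, two arms of equal size and no covariate. Let S be the control probability of staying unhealed through the interval and 1.40 the true HR. The Breslow estimate is then the risk ratio (1 − S^1.40) / (1 − S). The grouped-time estimate is ln(S^1.40) / ln(S) = 1.40 exactly.
- S = 0.9 (few heal): (1 − 0.863) / 0.1 = 1.37.
- Days 21-60, exponential healing, median 30 days: S = 2^(−1.3) = 0.406, giving (1 − 0.283) / 0.594 = 1.21.
- Days 21-60, Weibull shape 2, median 30 days: S = 2^(−3.51) = 0.088, giving (1 − 0.033) / 0.912 = 1.06.

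The more patients heal within one gap, the stronger the shrinkage. Efron ties reduce it but do not remove it. The value assigned inside the interval does not matter when visits are on schedule, because Cox regression uses only the order of times.

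**4. Simulation, true HR 1.39.** 304 patients 1:1, one baseline covariate, 300 replicates per row, two-sided 5% test. The Monte Carlo SE of power is up to about 2.9 points. The healing distribution and median are assumptions. The grouped-time model is a complementary log-log regression with one intercept per interval. Cells give HR (power).

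| Healing; visits; median | Exact times | Grouped-time | Midpoint, Efron | Midpoint, Breslow |
|---|---|---|---|---|
| Exponential; on schedule; 14 d | 1.399 (0.817) | 1.403 (0.780) | 1.354 (0.740) | 1.265 (0.540) |
| same; 21 d | 1.400 (0.800) | 1.405 (0.753) | 1.366 (0.733) | 1.277 (0.580) |
| same; 35 d | 1.398 (0.753) | 1.403 (0.733) | 1.380 (0.723) | 1.296 (0.590) |
| Exponential; dates vary by a few days; 14 d | 1.390 (0.780) | 1.390 (0.747) | 1.353 (0.707) | 1.334 (0.680) |
| same; 21 d | 1.389 (0.763) | 1.390 (0.740) | 1.361 (0.723) | 1.348 (0.713) |
| same; 35 d | 1.392 (0.717) | 1.396 (0.717) | 1.379 (0.710) | 1.370 (0.697) |
| Weibull shape 2; on schedule; 14 d | 1.398 (0.817) | 1.402 (0.737) | 1.309 (0.647) | 1.226 (0.430) |
| same; 21 d | 1.398 (0.817) | 1.406 (0.643) | 1.244 (0.493) | 1.189 (0.230) |
| same; 35 d | 1.399 (0.820) | 1.408 (0.693) | 1.285 (0.610) | 1.177 (0.183) |
| same; 40 d | 1.399 (0.800) | 1.404 (0.710) | 1.308 (0.627) | 1.189 (0.230) |

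With visits on schedule, dating healing at the first healed visit gave the same Efron estimates as the midpoint. At a true HR of 1.64 (1/0.61, another reading of the Nepal figure) with exponential healing, Efron gave 1.57-1.61 with power near 0.96.

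**5. A second set, true HR 1.40.** Across 18 combinations of assumptions, midpoint Cox was below the grouped-time model every time, and the grouped-time model returned 1.39-1.42. With Efron ties the estimate was about 1.35-1.41 under exponential healing and about 1.23-1.37 under Weibull shape 1.5-2. Breslow ties with exact-day visits gave about 1.17-1.29.

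**6. No effect.** At HR 1.0 (exponential healing) the midpoint estimates were 0.997-1.006. Rejection rates were 0.04-0.06 with Efron and 0.01-0.05 with Breslow.

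**The case against.** The strongest reply has four parts.

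- **The base case is mild.** With exponential healing and Efron ties, the HR is 1-3% low, and an interval-respecting model recovers only 1-4 points of power, close to simulation error. This stands for that scenario. Clustered healing is an assumption, but the protocol makes it plausible: the treatment review section says therapy often runs 4-6 weeks (days 28-42, inside the 21-60 gap), and the primary outcome section ties three months to typical healing time. Neither statement gives a healing distribution.
- **The worst figures need choices the protocol does not make.** A reader might infer that the plan as written cuts an HR of 1.40 to below 1.30 and loses a large part of the power. That needs Breslow ties on exact-day visits or strongly clustered healing. No tie method is named, and a separate analysis plan may fix one. Visit dates will also vary: Table 4 accepts three-week acuity from day 18 to week 5, and home visits are planned. Date variation rescues most of the Breslow result under exponential healing.
- **The midpoint rule is not the culprit.** Correct: the cause is grouping and ties. No analysis recovers the order of healing within an interval. A suitable model does remove the bias that comes from treating the times as exact.
- **The error is conservative and secondary.** Also correct. It cannot create a false claim of benefit, and the Fisher comparison of non-healing at three months does not depend on dating.

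What survives is that the protocol commits to a main model that ignores the interval structure. Naming Efron ties alone does not remove the bias when healing clusters in a wide gap.

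**Conclusion.** The point holds as a cheap improvement to a secondary outcome. If the arms differ, midpoint Cox on this schedule pulls the healing HR toward 1. For a true HR of 1.40, 304 patients and Efron ties, the estimate is about 1.35-1.41 under exponential healing, with about 0-4 points of power lost against the grouped-time model. It is about 1.23-1.37 under Weibull shape 1.5-2, with a loss from none to about 20 points. These ranges rest on an assumed healing distribution, median, tie method and spread of visit dates, none of which the protocol gives.

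Two stronger readings are not supported. A reader might infer that the authors judged the bias and dismissed it as small, but the protocol does not discuss bias from midpoint dating at all. A reader might also infer that the trial's main conclusion is at risk. The primary visual acuity analysis and the 304/358 sample size do not use healing times.

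**What to change.** In the Table 4 row, make the main healing analysis an interval-censored proportional hazards model with the same two covariates, arm and baseline ED size. Either form works:
- a complementary log-log regression with one intercept per visit interval, in which the chance of healing in interval j, if not yet healed, is 1 − exp(−exp(α_j + β·arm + γ·ED)) and exp(β) is the HR;
- an interval-censored model using each patient's actual dates of the last visit with a defect and the first without, which also copes with missed and shifted visits.

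Draw the curves with the Turnbull estimator in place of Kaplan-Meier on midpoints. Keep midpoint Cox as a sensitivity analysis and name Efron ties for it. The Fisher comparison at three months can stay as it is.

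The cost is a change of wording and a few lines of code, with no new data. The downside is a model less familiar to clinical readers; keeping the Cox result beside it helps comparison with other trials.

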Secondary outcomes listed in
Table 4 will be analyzed using regression models appropriate for the data type, adjusting for any baseline imbalances. 

**Table 4. T4:** Secondary Outcome Measures that will be investigated as part of the trial, together with analysis details.

Secondary outcome measure	Details
Three-week BSCVA	We will analyze the secondary outcome of three-week Best Spectacle-Corrected Visual Acuity (BSCVA) in logMAR using the same methodology applied to the primary analysis of the primary outcome. The three-week BSCVA assessment will include values recorded between 18 days and 5 weeks, with the closest value to 3 weeks being selected.
Presenting VA by Peek	The presenting visual acuity (VA) assessed using Peek Acuity, with and without pinhole, will also be analyzed as a secondary outcome at three months. This measure will be particularly relevant if reliable BSCVA readings cannot be obtained at three months (e.g., if patients do not attend the clinic and at-home visual acuity testing is required). This analysis will follow the same approach as the primary analysis of the primary outcome. A sensitivity analysis, incorporating data from participants lost to follow-up, will use the most recent recorded observation of this variable.
Scar/infiltrate size at 1 week, 3 weeks and 3 months by slit lamp examination.	For scar or infiltrate dimensions, the geometric mean of the two principal axes (in mm) will serve as the outcome variable at one week, three weeks, and three months. The scar size, observed via slit lamp, will be compared between treatment groups at each time point using linear regression. This will include treatment arm and baseline infiltrate/scar size as predefined covariates, controlling for baseline differences.

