Perforation and/or TPK and/or conjunctival advancement by three months (slit lamp examination by ophthalmic clinician)	The number of patients requiring perforation repair via Therapeutic Penetrating Keratoplasty (TPK), conjunctival advancement, or experiencing perforation itself by three months will be reported using confidence intervals and descriptive statistics. Since the study is not powered to detect significant differences in perforation or TPK rates, exploratory logistic regression analyses will estimate odds ratios for these outcomes between groups.
Loss of Eye	The proportion of patients requiring surgical removal of the eye (evisceration or enucleation) during follow-up will be described with confidence intervals. Logistic regression will explore treatment arm differences and associated risk factors.
Ocular adverse effects, slit lamp examination by ophthalmic clinician.	TThe occurrence of adverse events will be assessed by Fisher’s exact test. Poisson regression will compare adverse event rates, accounting for multiple events per participant.
Quality of life assessed using: EQ-5D, WHO/PBD-VF20, WHOQOL-BREF	QoL outcomes will be assessed using tools tailored to specific interests ^ 38 ^. Disease-related QoL will be evaluated with the WHO/PBD-VF20 (20-item Vision Function Questionnaire), which assesses the impact of visual impairment on mental well-being, dependency, and social functioning. For general health-related QoL, tools include the EQ-5D questionnaire, EQ-Visual Analogue Scale, and the WHOQOL-BREF. The EQ-5D provides standardized health outcome measures, while the WHOQOL-BREF evaluates four domains: Physical Health, Psychological Health, Social Relationships, and Environment. Scoring details for these tools are provided in Table 2. Comparisons of QoL scores between treatment groups will estimate the effects of chlorhexidine and natamycin. Adjustments will be made for variables like age, sex, socio-economic status, and recent health problems. Logistic, linear, and ordinal logistic regression methods will be employed depending on whether the outcome variables are binary, continuous, or ordered categorical. Mean scores and mean differences in QoL subscales and domains will be compared using t-tests and linear regression.

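### Treatment failure at three months is tested by Fisher's exact test with no covariate, although the plan's own rule and the same table row point to a regression on baseline defect size

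*Protocol article*

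**What the plan says.** Under Secondary outcome analysis, the sentence that introduces Table 4 says its outcomes "will be analyzed using regression models appropriate for the data type, adjusting for any baseline imbalances". The Table 4 row on time to full epithelial healing gives two analyses. Healing time goes into a Cox model with treatment group and "baseline ED size (geometric mean in mm) included as a covariate". The row then closes with treatment failure, meaning a defect above 0.5 mm at three months, which "will be compared between groups using Fisher’s exact test". No covariate is named for that last comparison.

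The other binary clinical outcomes in the table are handled differently. Microbiological cure at day 7 uses logistic regression adjusted for organism type. Perforation or surgery by three months, and loss of the eye, also use logistic regression.

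The only significance level in the Analysis plan belongs to the primary outcome: "Significance will be assessed using a two-tailed test at 0.0492 level for assessing superiority". No level, event rate or power is given for treatment failure.

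**The concern.** Failure is the persistence at three months of the same epithelial defect that is measured at baseline, so baseline size is an obvious candidate predictor. The row uses it for time to healing and then drops it for failure, without giving a reason and against the general sentence above the table.

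Two separate costs follow. First, the event total is not fixed by this design, so Fisher's test, which conditions on that total, rejects less often than its nominal level. Second, a test on the plain two-by-two table cannot adjust for a chance imbalance in baseline defect size and gives up whatever power the covariate would add. Both make a real difference in failure to heal easier to miss. Neither can create a false positive finding.

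**Working it through.** **Number per arm.** Sample size considerations gives a difference of 0.2 logMAR, "a standard deviation of 0.62 in both groups", alpha 0.0492 and 80% power. Per arm:

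n = 2 × (1.9669 + 0.8416)² × (0.62 / 0.2)² = 2 × 7.888 × 9.61 = 151.6, so 152 per arm and 304 in all.

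304 / 0.85 = 357.6, so 358. Both of the plan's figures reproduce. I use 152 per arm, because failure is judged at the same three-month visit as the primary outcome.

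**Assumptions.** Two-sided 0.05 for this outcome, and failure rates from 10% to 25%. The document gives neither.

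**Cost of discreteness.** For each pair of counts (x, y) out of 152, compute the p-value. Then sum Bin(x; 152, p₁) × Bin(y; 152, p₂) over all pairs with p ≤ 0.05. This is exact.

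| Failure rates | Quantity | Fisher | Pearson chi-squared |
|---|---|---|---|
| 10% both arms | size | 3.3% | 5.0% |
| 20% both arms | size | 3.6% | 5.1% |
| 25% both arms | size | 3.7% | 5.1% |
| 20% v 10% | power | 63.7% | 69.3% |
| 25% v 12.5% | power | 76.3% | 80.8% |

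The loss is 69.3 − 63.7 = 5.6 points in the first power row and 80.8 − 76.3 = 4.5 points in the second.

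**Cost of omitting the covariate.** This was simulated with 3,000 runs per setting and 152 per arm. The test is a likelihood ratio test of arm in a logistic model with one standard normal covariate, whose odds ratio per SD is assumed to be 1.5, 2 or 3.

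| Failure rates | Fisher (same runs) | Adjusted logistic |
|---|---|---|
| 20% v 10% | 64.1%, 62.3%, 63.4% | 71.7%, 71.0%, 75.5% |
| 25% v 12.5% | 75.3%, 75.9%, 77.9% | 81.2%, 82.9%, 87.4% |

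Monte Carlo standard error is about √(0.72 × 0.28 / 3000) = 0.8 points. Against the exact chi-squared power, adjustment adds about 2 to 6 points at 20% v 10% (for example 75.5 − 69.3 = 6.2) and about 0 to 7 points at 25% v 12.5% (87.4 − 80.8 = 6.6). Against Fisher's test the total gain is about 6 to 12 points.

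In the null runs (25% and 10% in both arms) the adjusted test had size 4.9% to 5.8%, standard error 0.4 points. It may therefore be slightly liberal at the 10% rate, and a small part of its apparent gain could come from that.

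**The case against.** Fisher's test controls the type I error, so the choice can be defended as cautious. The row's principal analysis is the Cox model, which already adjusts for baseline defect size; failure is a closing comparison in a trial not powered for it. The sentence above Table 4 also reads as a summary, because other rows depart from it: costs use t-tests and adherence uses descriptive statistics. All of this stands and keeps the point minor. It does not remove it: the Cox model does not test the proportion unhealed at three months, and the other binary clinical outcomes do follow the regression rule.

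Three stronger readings do not hold.

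- A reader might infer that leaving out the covariate lowers the true error rate. It does not. The unadjusted chi-squared test has size 5.0% to 5.1% in the table above. The low size comes from discreteness; the covariate affects power and balance.
- A reader might infer that a stated 5% test is really a 1% to 4% test. No level is stated for secondary outcomes, and sizes near 1% arise only for rare events (1.2% at a 2% rate).
- A reader might extend the point to the safety row, where the "occurrence of adverse events will be assessed by Fisher’s exact test". That row continues: "Poisson regression will compare adverse event rates, accounting for multiple events per participant", so harm does not rest on Fisher's test alone. For 5% v 1%, chi-squared power is 54% against 40% for Fisher at 152 per arm, but with about 0.03 × 152 = 4.6 events expected per arm, an exact test is a reasonable choice. An unconditional exact test (Boschloo) gives 46.5% v 40.4% at 152 per arm and 51.4% v 49.7% at 179, a gain of roughly 6 and 2 points. That is a choice between valid tests and not a fault in the plan.

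**Conclusion.** The point holds for treatment failure only, as a minor matter of efficiency and internal consistency in a secondary outcome. With 152 per arm, an assumed nominal 5% and failure rates of 10% to 25%, Fisher's test has a true size of about 3.3% to 3.7% and gives up about 5 points of power to the chi-squared test. Omitting baseline defect size costs a further 0 to 7 points if the covariate is as prognostic as assumed, and leaves any chance imbalance in it unadjusted. The document supplies neither the failure rates nor the covariate's strength, so these figures show scale and are not predictions. The primary analysis is untouched.

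**What to change.** In the Table 4 row on epithelial healing, replace Fisher's test for treatment failure with logistic regression on treatment arm and baseline epithelial defect size. Report the odds ratio and a standardised risk difference, each with a 95% confidence interval. Keep Fisher's test only as a named fallback if failures are too few to fit the model, and state in advance what count triggers it. Leave the adverse event row as it is.

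The cost is a change of wording in one table row and a few lines of code. Baseline defect size is already measured and already used in that row, so no new data are needed.
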